## 2. Problem Statement and Justification

Patients under mechanical ventilation (MV) in the intensive care unit (ICU) exhibit high hospital mortality rates, ranging from 23% to 51%. This mortality is linked to the success of weaning and the incidence of nosocomial infections. Prolonged MV can increase complications in critically ill patients, extending immobility and raising the risk of ventilator-associated pneumonia, further restricting patients. It is argued that early mobility improves MV-related outcomes, such as ventilator duration and ventilator-free days, breaking the vicious cycle of prolonged MV and immobilization. Additionally, early rehabilitation is associated with reduced morbidity and mortality, as well as complications of the disease, ICU length of stay, hospital stay, and rehospitalization rate. Therefore, weaning from MV through early rehabilitation is crucial to improving the prognosis of ICU patients.

Despite the growing evidence on the utility of early rehabilitation for critically ill patients, programs and interest in outcomes vary among studies. Given this diversity, healthcare professionals must assess whether different programs have a similar therapeutic effect and ensure that the prescribed rehabilitation provides benefits consistent with previous literature. Besides the heterogeneity among programs, different countries and institutions face barriers to implementation, such as a shortage of trained rehabilitation personnel and a cultural gap in the ICU. In cases of personnel

shortages and settings with conservative ICU ethics, early rehabilitation is adapted to a sustainable level, including modified programs or less frequent visits.

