| Comparator | Late multimodal therapy is defined as the initiation of multimodal therapy 3 days or more after the start of mechanical ventilation. The comparator differs from the study intervention only in the moment (time from orotracheal intubation to the start of multimodal therapy) of initiation of therapy.                                                                                                                                                                                                                                                                                                                                                                                                                                                                                                                                                                                                                                                                                                                                      |
| Outcomes   | 
Effectiveness
 
Primary outcome: Number of days with invasive mechanical ventilation in the ICU
 
Secondary outcomes:
 
 
• Days free of mechanical ventilation until day 28
 
• Days of delirium until day 28
 
• Time in ICU with delirium until day 28
 
• Days of hospitalization with delirium until day 28
 
• Sedation days until day 28
 
• Sedation-free days until day 28
 
• Barthel index at discharge
 
• Days of hospital stay
 
• Length of stay in ICU
 
• Mortality from any cause up to 90 days
 
• Time from intubation to start of therapy
 
• Muscle strength measured with the medical research scale council (MRC)
 
• Dysphagia at 72 hours
 
• Time until initiation of oral administration
 
• Development of healthcare-associated pneumonia,
 
• Maximum mobility measured by JH-HLM
 
• Grip strength
 
• Extubation failure
 
 |

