### Specific Objectives:

- To describe the sociodemographic and clinical characteristics of patients with invasive mechanical ventilation in the Neurological Intensive Care Unit at Fundación Santa Fe de Bogotá.
- To evaluate the efficacy of early multimodal therapy versus late multimodal therapy in terms of ventilator-free days and other secondary outcomes.

- To establish the sociodemographic and clinical factors associated with the type of therapy (early or late) the primary outcome (ventilator-free days) and secondary outcomes.
- To evaluate the safety of early multimodal therapy versus late multimodal therapy in terms of adverse events, serious adverse events, episodes of broncho-aspiration, and healthcare-associated pneumonia.
- To evaluate the impact of different predefined subgroups, such as the type of respiratory failure (hypoxemic or hypercapnic) and the type of patient (surgical, respiratory, burn, cardiovascular), on the primary outcome results.

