## 6.6. Outcomes

### *Effectiveness*

Main outcome: time (days) from intubation to extubating.

- Secondary outcomes:

- Days free of mechanical ventilation until day 28
- Days of delirium until day 28
- Time in ICU with delirium until day 28
- Days of hospitalization with delirium until day 28
- Days of sedation until day 28
- Sedation-free days until day 28
- Extubating failure
- Need for non-invasive mechanical ventilation
- Exploratory outcomes:
- Barthel index at discharge
- Days of hospital stay
- Length of stay in ICU
- Mortality from any cause up to 90 days
- Time from intubation to start of therapy
- Muscular strength measured with the Medical Research Council (MRC) scale
- Dysphagia 72 hours after extubation
- Dysphonia 72 hours after extubation
- Time until initiation of oral administration post-extubation
- Development of healthcare-associated pneumonia,
- Maximum mobility measured by JH-HLM
- Grip strength
- Cognitive function measured using the Montreal Cognitive Assessment (MOCA)
- Evaluation of functionality in daily activities until day 28
- Quick sensitivity and dexterity test

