| Days from the start of ventilatory support to the start of weaning | Days from the start of ventilatory support (intubation) to the start of weaning                                                                                                                   | Discrete Quantitative   | Days                                                                                                                                                                                                     |
| Days of mechanical ventilation                                     | Days of invasive mechanical ventilation                                                                                                                                                           | Discrete Quantitative   | Days                                                                                                                                                                                                     |
| Days free of mechanical ventilation                                | 28 days minus ventilation days                                                                                                                                                                    | Discrete Quantitative   | Days

It will be defined as 0 if the patient dies or has been ventilated for more than 28 days.                                                                                                    |
| Delirium                                                           | For a patient to be considered to have delirium according to the CAM-ICU, both the first criterion (acute alteration in mental status) and at least one of the other three criteria (inability to | Qualitative Nominal     | 
 
1. Acute alteration of mental status (+/-).
 
2. Inability to maintain sustained attention (+/-).
 
3. Disorganization of thought (+/-).
 
 |

|                                          |                                                                                                                                |                       |                                                        |
|------------------------------------------|--------------------------------------------------------------------------------------------------------------------------------|-----------------------|--------------------------------------------------------|

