### 6.13. Statistical Analysis Plan

A Shapiro-Wilk test will be conducted to verify the distribution of quantitative variables, considering the number of patients included. Data will be presented as means or medians, accompanied by their standard deviation or interquartile range, as appropriate. Categorical variables will be described as absolute and relative frequencies.

To compare continuous variables between the two groups (early vs. late therapy), a T-test or the Mann-Whitney U test will be employed, depending on the distribution of the data. For categorical variables, a  $\chi^2$  test or Fisher's exact test will be used, as appropriate.

The primary objective of the study is to evaluate the association between the use of early multimodal therapy and the days of invasive mechanical ventilation. To address this question, we will perform a survival analysis and a Cox regression. A risk variable will be created by combining the time of invasive mechanical ventilation and extubation (yes/no). Then, a univariable Cox regression analysis will be performed with the risk variable as the dependent variable and the intervention group (early vs. late) as the independent variable. Additionally, a survival curve will be generated, and differences between the two groups will be analyzed using a log-rank test.

To evaluate factors related to the time of mechanical ventilation, univariable Cox regression models will be performed for all variables included in the study. To determine whether continuous variables can be evaluated continuously or as categorical variables, the assumption of linearity will be checked through the Martingale residual plot. If linearity is not met, the variable will be stratified, and cut-off points will be defined according to the appearance of the plot. Subsequently, those variables with a statistically significant p-value (less than 0.25) and clinically important variables (age, sex, delirium, etc.) will be included in a multivariable Cox regression model. The best model will be selected through a Backward Stepwise process based on Akaike (AIC) and Bayesian (BIC) information criteria.

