#### During observation:

To register of shape suitable for these data must pass all the days to appreciate the patient.

- Days of Mechanical Ventilation: \_\_\_\_\_ (date of start-end date)

- Days Free from Mechanical Ventilation: \_\_\_\_\_(calculated the final of the observation)
- Days of Delirium: \_\_\_\_\_( start date - end date)
- Days of Hospitalization with Delirium: \_\_\_\_\_(calculated the final of the observation)
- Sedation Days: \_\_\_\_\_(date of start- date of ending)
- Days Free from Sedation: \_\_\_\_\_(calculated the final of the observation)
- Prolonged Mechanical Ventilation: \_\_\_\_\_(Yes/No)
- Tracheostomy: \_\_\_\_\_(Yes/No).
- Syndrome of Difficulty Respiratory of the Adult: \_\_\_\_\_(Yes/No)
- Presence of pneumonia associated with the Careful of health: \_\_\_\_\_(Yes/No)
- Need dialysis: \_\_\_\_\_(Yes/No)
- Medium with norepinephrine \_\_\_\_\_(Yes/No)
- Support with vasopressin \_\_\_\_\_(Yes/No)
- Medium with inotrope \_\_\_\_\_(Yes/No)
- Dose maximum of norepinephrine \_\_\_\_\_( mcg /kg/min)
- Maximum dose of vasopressin \_\_\_\_\_(IU/min)

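### The primary analysis censors deaths on the ventilator by its coding, the primary outcome has no death or reintubation rule, and one objective names a different primary outcome

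*Protocol*

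**What the plan says.** **Analysis.** Section 6.13 assigns to the primary objective a univariable Cox model on treatment group. Its outcome is described as "A risk variable will be created by combining the time of invasive mechanical ventilation and extubation (yes/no". In addition, "a survival curve will be generated, and differences between the two groups will be analyzed using a log-rank test". A separate, general line compares continuous variables by t-test or Mann-Whitney.

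**Name of the primary outcome.**
- Section 3 (PICOT table): "Primary outcome: Number of days with invasive mechanical ventilation in the ICU".
- Section 6.6: "Main outcome: time (days) from intubation to extubating".
- Section 5, in the specific objective on associated factors: "the primary outcome (ventilator-free days". The Summary has the same objective with equivalent wording. Sections 3 and 6.6 both list ventilator-free days as secondary.

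**Death.** Section 2 describes ventilated ICU patients as having "high hospital mortality rates, ranging from 23% to 51" per cent. For ventilator-free days the variable table in section 6.11 states: "It will be defined as 0 if the patient dies or has been ventilated for more than 28 days". Sedation-free days, Barthel, JH-HLM and grip strength are also set to 0 at death. The entry for days of mechanical ventilation has no such rule.

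**Decision rule.** Section 6.10 says that the trial could be considered a failure if mean duration of mechanical ventilation does not differ significantly between arms.

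**Failed extubation.** Failure at 48 hours is collected (sections 6.7 and 6.11, Annex 5) as a separate yes/no variable. It is not linked to the primary event.

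**The concern.** Death on the ventilator prevents extubation and also ends ventilation. An analysis of ventilation time has to say which of these it reflects, and the protocol does not.

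Three things follow. A survival curve that censors deaths estimates extubation as if nobody died. A hazard ratio for extubation alone says nothing about whether more patients died before reaching it. Raw ventilation days record an early death as a short, favourable duration. If early therapy changed mortality, the candidate primary measures could point in opposite directions. Because the documents do not name one measure consistently, the choice could be made after the results are known.

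**Working it through.** The protocol gives no figure of its own on this point, so there is nothing to reproduce. The check has three steps.

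**1. Coding.** Time is ventilation time; status is extubation yes or no. Death while intubated gives status = no at the time of death, which Cox, log-rank and an ordinary survival curve all treat as censoring. The protocol never uses the word; censoring is the direct consequence of the coding.

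**2. Size, in closed form.** All hazards are assumptions; none is in the protocol. Let a = 0.14/day (extubation, the same in both arms, so no true effect on extubation), d = daily hazard of death on the ventilator, L = a + d, horizon 28 days, and E = 1 − exp(−28L). Deaths after extubation are ignored.

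- Mean ventilation days = E/L
- Extubated alive by day 28 = (a/L)·E
- Death on the ventilator = (d/L)·E
- Mean ventilator-free days (death = 0) = a·[28/L − E/L²]
- Survival-curve estimate of extubation with deaths censored = 1 − exp(−28 × 0.14) = 1 − exp(−3.92) = 98%, whatever d is

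Late arm, d = 0.04, L = 0.18, E = 0.9935: mean days 0.9935/0.18 = 5.5; extubated 0.7778 × 0.9935 = 77%; ventilator-free days 0.14 × (155.56 − 30.66) = 17.5.

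Early arm, d = 0.08, L = 0.22, E = 0.9979: mean days 0.9979/0.22 = 4.5; extubated 0.6364 × 0.9979 = 64%; ventilator-free days 0.14 × (127.27 − 20.62) = 14.9.

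The late arm stays at d = 0.04 (second row) while the early-arm death hazard varies:

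| Early-arm d | Died on ventilator | Mean ventilation days | Extubated alive | Ventilator-free days | Curve with deaths censored |
|---|---|---|---|---|---|
| 0.02 | 12% | 6.2 | 87% | 19.1 | 98% |
| 0.04 (equals late arm) | 22% | 5.5 | 77% | 17.5 | 98% |
| 0.06 | 30% | 5.0 | 70% | 16.1 | 98% |
| 0.08 | 36% | 4.5 | 64% | 14.9 | 98% |

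The cause-specific hazard ratio for extubation is 0.14/0.14 = 1.00 in every row. More deaths shorten raw days and fewer deaths lengthen them, so the distortion runs both ways. With equal death hazards the arms agree on every measure, but the curve still shows 98% extubated where the true figure is 77%.

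**3. When sicker patients are the ones who die.** A simulation used a mean time to extubation of 6.1 days (the usual-care mean in section 6.3) and again no true effect on extubation. It assumed early-arm death hazards two to three times those of the late arm.

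- Death independent of readiness for extubation, hazard doubled: deaths on the ventilator 23% versus 38%; raw days 4.66 versus 3.79; Cox HR with deaths censored 1.00; subdistribution HR 0.75; ventilator-free days 17.9 versus 15.1.
- Shared frailty (SD 0.7 to 1), hazard doubled: Cox HR 1.05 to 1.08; with the hazard tripled at SD 1, 1.12. Subdistribution HRs were 0.75 to 0.84.
- At 37 per arm, the chance of a nominally significant result favouring early therapy (nominal 2.5%) was about 3% to 6% for log-rank and about 11% to 22% for Mann-Whitney on raw days.

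**Failed extubation, illustration only.** Assume the early arm is extubated at 1.3 times the rate, reintubation is 25% versus 2%, and each reintubation costs 5 extra days. Mean time to first extubation is 6.1 (late) versus 6.1/1.3 = 4.7 (early). Total ventilation days are 6.1 + 0.02 × 5 = 6.2 versus 4.7 + 0.25 × 5 = 5.9. Most of the apparent gain depends on which definition is used.

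**The case against.** **Cox regression with deaths censored is a legitimate analysis.** It estimates the cause-specific hazard of extubation. This stands. The fault is presenting it alone, with a survival curve and without the matching hazard for death.

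**A reader might infer that the primary test turns death into benefit.** The protocol does not support that. With death independent of readiness for extubation, the hazard ratio stays at 1.00: harm is hidden and no benefit is created. False benefit in the Cox model needs sicker patients to be the ones who die, and it is then modest. The t-test or Mann-Whitney line in section 6.13 is general and is not assigned to the primary objective. Raw days matter because section 6.10 judges the trial on them.

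**Harm would appear elsewhere.** Ventilator-free days with death = 0, 90-day mortality and serious adverse events are all reported. This stands, but section 6.6 places the first among the secondary outcomes and mortality among the exploratory ones, so they do not repair the primary comparison.

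**The scenario may be unlikely.** The 23% to 51% is general hospital mortality, not death on the ventilator in patients with Barthel of at least 70 and with cardiac arrest and short life expectancy excluded. Section 4 reports no mortality difference in a 750-patient trial and none at 28 days in a meta-analysis, although that trial had more serious adverse events with early mobilisation. The doubled hazard therefore shows the mechanism and is not a forecast.

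**The naming conflict is narrow.** The research question, general objective, hypotheses, sample size and section 6.13 all concern ventilation duration; the contradiction lies in one specific objective that appears twice. This stands.

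**A reader might infer that the data form cannot show why ventilation ended**, because ventilation days are entered as "date of start-end date". Annex 5 also records tracheostomy, failed extubation, mortality and unscheduled extubation, and section 6.11 lists days to death. The reason can largely be reconstructed.

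**Conclusion.** The point holds in a limited form. By its coding the primary analysis censors deaths on the ventilator, and no death rule is given for the primary outcome. The curve overstates extubation (98% against 77% or 64% in the worked case), and the Cox and log-rank result can miss a mortality harm. A false benefit in the Cox model requires informative death and is small under the assumptions tried (HR about 1.05 to 1.12). The larger false benefit is in raw days: 1.0 day fewer in the early arm (5.5 versus 4.5) while ventilator-free days are 2.6 lower (17.5 versus 14.9).

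These sizes rest on assumed hazards and on a difference in death hazard between arms; without that difference, the distortion between arms vanishes. The conflicting name for the primary outcome and the silence on reintubation do not themselves create bias, but they leave open which quantity is being tested. Section 6.13 fixes this analysis in the protocol itself, so it is not a detail left to a separate plan. It should be corrected before outcome data are seen.

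**What to change.** 1. Name one primary outcome in the Summary and in sections 3, 5, 6.6 and 6.13, and correct the specific objective that calls ventilator-free days primary.
2. Replace the survival curve with cumulative-incidence curves in which death on the ventilator is a competing event. Report the cause-specific hazard ratios for extubation and for death together.
3. Name the primary test in advance. A Gray or Fine-Gray comparison, or 28-day ventilator-free days with death = 0, is acceptable; neither is the only correct choice.
4. State that an extubation counts as the event only if there is no failure within the 48 hours already collected, and state how ventilation through a tracheostomy is counted.
5. In section 6.10, replace raw mean duration with the chosen measure that accounts for death.

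The cost is protocol wording, slightly more analysis work and an effect measure less familiar to clinicians. The variables already listed should largely suffice.

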#### 6.11. Data Collection

**Variable description:**

| Variable                | Definition                           | Variable type           | Scale/Unit
measurement
categories
of
or  |
|--------------------------------|---------------------------------------------|--------------------------------|-----------------------------------------------------------------------|
| Age                            | Years old                                   | Quantitative

Discreet   | Years                                                                 |
| Weight                         | Weight                                      | Quantitative

Keep going | Weight in kilograms                                                   |
| Sex                            | Sex                                         | Qualitative
Nominal         | Female or male                                                        |
| Ethnicity                      | Ethnicity with which the patient identifies | Qualitative
Nominal         | Afro-Colombian

ROM

Indigenous

Raizal

None |
| Dialysis                       | Need for renal replacement therapy          | Binomial
Categorical        | 0: No

1: Yes                                                   |
| Norepinephrine support         | Need for norepinephrine support             | Binomial
Categorical        | 0: No

1: Yes                                                   |
| Maximum dose of norepinephrine | Dose in mcg/kg/min                          | Quantitative
continues      | Mcg /kg/min                                                           |
| Inotropic support              | Need for inotropic support                  | Binomial
Categorical        | 0: No

1: Yes                                                   |

|                             |                                                                                                                                                                                                         |                            |                                   |

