| Dysphagia 72 hours after extubation                     | Dysphagia 72 hours after extubation                                               | Qualitative Nominal | Yes or no                                                                                                                                                                                                                                                                                                                                                                                                                                                                       |
| Oral start time.                                        | Time in which the oral route is started after extubation.                         | Qualitative Nominal | 
1: 12-24 hours
 
2: > 24 hours
                                                                                                                                                                                                                                                                                                                                                                                                                                   |
| Healthcare-associated pneumonia                         | The patient developed healthcare-associated pneumonia during his stay in the ICU. | Nominal qualitative | 
0 = No
 
1 = Yes
                                                                                                                                                                                                                                                                                                                                                                                                                                                    |

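### The factor models for time to extubation accept every study variable with no timing rule, so undated events that arise during ventilation will look as if they delay extubation

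*Protocol*

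**What the plan says.** Section 6.13 (repeated in the Summary) builds the survival outcome from time on invasive ventilation, with extubation as the event. For the aim "To evaluate factors related to the time of mechanical ventilation", it states that "univariable Cox regression models will be performed for all variables included in the study". Variables with p below 0.25 move on to a multivariable model, and the plan adds that "clinically important variables (age, sex, delirium, etc.) will be included in a multivariable Cox regression model". Backward selection by AIC and BIC follows.

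The section 6.11 variable table defines several of these variables as events of the ICU course:

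- Pneumonia is 0/1: "The patient developed healthcare-associated pneumonia during his stay in the ICU".
- Dialysis is 0/1: "Need for renal replacement therapy".

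Annex 5 lists both under its heading for the observation period as Yes/No, with no onset date. Norepinephrine, vasopressin and inotrope support, tracheostomy and ARDS are recorded the same way. Delirium is different: section 6.7 and Annex 5 ask for its start and end dates.

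The Cox checks named in 6.13 are martingale plots for linearity, Schoenfeld residuals, influence plots and collinearity. The section mentions no time-dependent covariate, no landmark analysis and no restriction to baseline variables.

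**The concern.** A yes/no code for something that happens during ventilation is not a baseline characteristic. Entered as a single value, it labels the patient as exposed from intubation, including the days before the event. To be labelled at all, the patient must still have been ventilated when the event occurred. The code therefore partly measures the outcome, which is immortal-time bias. It pushes the hazard ratio for extubation below 1 even when the event has no effect.

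Read literally, the word covering all variables also admits items that cannot be predictors. Dysphagia and dysphonia at 72 hours after extubation, and failed extubation, are known only after the event being modelled. Prolonged ventilation and days of ventilation are the outcome itself.

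At stake is the factor analysis. Its univariable hazard ratios and p-values would be biased, and the p-values feed the 0.25 screen. None of the named checks corrects this: they examine functional form, proportionality, influence and collinearity, not the date at which exposure began. The multiplicity adjustment in 6.13 does not repair a biased estimate.

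**Working it through.** The plan states no figure to reproduce. The check has two parts.

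**Inputs.** From the protocol: 37 patients per arm, 74 in total; ventilation 6.1 days (SD 1.4) with usual therapy and 3.4 days (SD 1.25) with early therapy (section 6.3). Assumed, because the protocol gives no event rates: onset at a constant daily rate, independent of extubation (true hazard ratio 1), and no deaths or censoring.

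**Mechanism by arithmetic.** With onset rate r per day, a patient ventilated T days scores yes during ventilation with probability 1 − exp(−rT).

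| r per day | T = 3.4 days | T = 6.1 days |
|---|---|---|
| 0.03 | 1 − exp(−0.102) = 9.7% | 1 − exp(−0.183) = 16.7% |
| 0.06 | 1 − exp(−0.204) = 18.5% | 1 − exp(−0.366) = 30.6% |
| 0.25 | 1 − exp(−0.850) = 57.3% | 1 − exp(−1.525) = 78.2% |

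The event does nothing, yet it is commoner in the patient ventilated longer.

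**Simulation.** Normal ventilation times with the section 6.3 means and SDs, 300 or 400 replicates per setting, fixed yes/no coding:

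| Onset per day | Patients affected | Median HR | p<0.05 | p<0.25 |
|---|---|---|---|---|
| 1% to 3% | 5% to 13% | 0.73 to 0.76 | 4% to 10% | 28% to 38% |
| 5% | 21% | 0.71 | 20% | 52% |
| 6% | 24% | 0.69 | 24% | – |
| 10% | 37% | 0.65 | 39% | 73% |
| 25% | 66% | 0.52 | 72% | – |

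A separate run over 3% to 25% per day gave HR 0.72 to 0.51 and 13% to 69% at p<0.05. When the covariate switched on at onset in the same setting, the HR was about 1, with 6% to 8% at p<0.05.

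**Sensitivity to the spread of ventilation times.** Same means, but a 1-day minimum plus exponential or Weibull (shape 1.5) times, onset 2% to 15% per day:

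- Fixed coding: HR 0.59 to 0.37, and 20% to 98% at p<0.05.
- Time-dependent coding: HR 0.98 to 1.04, and about 4% to 7.5% at p<0.05.

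**Sensitivity to events counted after extubation.** Events counted up to 3 days after extubation, exponential times, onset 5% to 10% per day: HR 0.58 to 0.54, against 0.46 to 0.43 when only ventilated time counts. The bias shrinks but stays.

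**The case against.** - **The protocol never says these variables enter as fixed covariates.** True. A reader might infer that the plan prescribes fixed coding throughout; it does not. For delirium, the dates would allow time-dependent coding. For the undated items, a single yes/no leaves no other coding unless dates are recovered from the daily records, and the plan does not say that they will be. This is more than a detail left to a separate SAP, because 6.13 itself decides which variables enter and names delirium.
- **Not every listed event must start during ventilation.** This also stands. Dialysis or delirium may be present before intubation, and pneumonia is counted over the whole ICU stay. The bias applies to the share of events that begin while the patient is ventilated.
- **The word covering all variables is loose drafting.** Section 6.13 uses failed extubation, post-extubation NIV, prolonged ventilation, tracheostomy and dysphonia as outcomes in logistic models. That suggests the literal reading was not intended, but it does not remove them from the Cox screen.
- **The objective concerns a different endpoint.** The specific objective "To establish the sociodemographic and clinical factors associated with the type of therapy (early or late) the primary outcome" goes on to name ventilator-free days in brackets, so it is a weak anchor. The stated purpose in 6.13 is time on mechanical ventilation, and that is enough. Both texts speak of association, so one cannot say the trial will declare these events to be causes.
- **The size rests on assumed inputs.** Correct. With the protocol's SDs and rare events, the excess of false positives at 5% is small. A hazard ratio near 0.40 and 94% false positives were seen with an assumed SD of 3.5 days, not with the protocol's SDs.

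**Conclusion.** The point holds for the secondary factor analysis. Followed as written, 6.13 gives hazard ratios biased towards apparent delay of extubation for any undated event that arises during ventilation. With the section 6.3 means and SDs and an assumed onset of 3% to 25% per day, the median hazard ratio for a harmless event is about 0.72 to 0.51, with roughly 10% to 70% false positives at 5%. The bias is larger if ventilation times are more spread out than those SDs. For rare events it is small in false-positive terms, although the hazard ratio still sits below 1. The direction was the same in every setting; the size depends on onset rates that the protocol does not give.

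A reader might infer that the trial's main result is compromised. The document does not support that: the primary univariable Cox model by arm and the log-rank test use none of these variables. The change should be made, but it does not threaten the primary comparison.

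**What to change.** In section 6.13, and in the matching Summary text:

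1. Limit the time-to-extubation factor models to variables known at intubation or randomisation. This needs no new data fields. It also removes counts and maxima that build up over the stay, such as sedation days, delirium days and maximum vasopressor dose, which a simple switch-on indicator would not handle.
2. Drop variables measured after extubation or derived from ventilation time: dysphagia and dysphonia at 72 hours, failed extubation, prolonged ventilation and days of ventilation.
3. If an in-ICU event is kept as a factor, enter it as a time-dependent covariate that switches on at its onset date. Delirium dates are already collected. For each other event kept (pneumonia, dialysis, vasopressors, inotropes, tracheostomy, ARDS), add an onset date to Annex 5.

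The cost is either fewer candidate factors, or one date field per event kept and slightly more programming. No extra patients or visits are needed. If dates are wanted, they are best captured prospectively, since adding them later would mean chart review.
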